#### Missing data

For our primary analysis, we will use multiple imputation to impute missing covariates using 15 imputations and setting the random seed at 300.^14^ We will use Stata’s *mi chained* command to perform the imputation. We will also perform sensitivity analyses to determine the potential impact of missing outcome data by looking at worst case scenarios (ie, all missing participants with missing outcome data achieved the lowest grade/highest grade possible).

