## Abstract

**Introduction:**

The effect of infant nutrition on long-term cognition is important for parents and policy makers. However, most clinical trials typically have short follow-up periods, when measures of cognition are poorly predictive of later function. The few trials with longer-term follow-up have high levels of attrition, which can lead to selection bias, and in turn to erroneous interpretation of long-term harms and benefits of infant nutrition. We address the need for unbiased, long-term follow-up, by linking measures of educational performance from administrative education records. Educational performance is a meaningful marker of cognitive function in children and it is strongly correlated with IQ. We aim to evaluate educational performance for children who, as infants, were part of a series of trials that randomised participants to either nutritionally modified infant formula or standard formula. Most trialists anticipated positive effects of these interventions on later cognitive function.

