### Outcomes

#### Primary outcome

At age 16 years (during Key Stage 4), English pupils take their General Certificate of Secondary Education (GCSE). The primary outcome for this study will be the mean difference in GCSE mathematics exam z-score between control and intervention groups. GCSE mathematics exams are compulsory, nationally administered and are graded from 58 points to 0 point (table 1).

**Table 1 T1:** GCSE grade structure during analysis period (2001–2016)

Grade	Points equivalent	Remarks
A*	58	Highest pass
A	52	
B	46	
C	40	
D	34	
E	28	
F	22	
G	16	Lowest pass
U	0	Ungraded

GCSE, General Certificate of Secondary Education.

We chose Mathematics over English, which is also compulsory and nationally administered, because exam results for mathematics are commonly considered to be less subjectively graded.^11^ We chose the primary endpoint at age 16 rather than age 11 as it is a more relevant predictor of future education and employment opportunities. Children who have not yet attended Key Stage 4 at the time of linkage will not be included in the primary outcome.

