#### Power

The primary outcomes (mean difference in z-score of Mathematics exam at age 16) will be continuous and analyses will be conducted for each trial separately. We expect primary outcomes to be available for around 70% of the original cohort with an equal retention rate in treatment and control arms. A 0.1 SD difference (this corresponds to one-fifth of a GCSE grade or 1.154 points on the 58 points point scale) will be regarded as clinically significant.^19 20^ The desired power to detect a difference between the treatment arms that is at least as large as this is 80% with a significance level of 0.05. The R-squared is expected to be 0.05–0.1. Taking the 1993/95 LCPUFA term study (n=309) as an example, a conservative 50% (n=154) linkage success would enable a detection of 0.45 SD difference (eg, 9/10 of a grade or 5.193 grade points).

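### The worst-case analysis for missing GCSE mathematics gives both arms the same extreme grade, so it does not test whether unobserved grades differ between arms

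*Protocol article*

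**What the plan says.** The Missing data section of the protocol article uses multiple imputation for missing covariates. For missing outcomes it promises sensitivity analyses "to determine the potential impact of missing outcome data by looking at worst case scenarios", and explains that these take it that "all missing participants with missing outcome data achieved the lowest grade/highest grade possible". No arm is mentioned.

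The Power section states: "We expect primary outcomes to be available for around 70% of the original cohort with an equal retention rate in treatment and control arms". It also gives a worked example at 50% linkage, which it labels conservative.

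The Primary outcome section says that GCSE mathematics is "graded from 58 points to 0 point", so the two filled values are 0 and 58. The Secondary outcomes section divides every z-score by the pooled within-trial SD. It does not say whether that SD is recalculated once missing values are filled.

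The Assessment of bias section compares pre-randomisation characteristics between arms, at randomisation and at age 16.

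**The concern.** A worst case for a treatment comparison should show how far the missing outcomes could move the difference between arms. Giving every missing child the same grade, whichever arm the child was in, fixes the arm difference among the missing at zero. That is one benign assumption, applied twice with different filled values.

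This matters more here than in most trials because avoiding attrition bias is the reason for the study. The Abstract says of previous work: "The few trials with longer-term follow-up have high levels of attrition, which can lead to selection bias". About 30% of primary outcomes are nevertheless expected to be missing, and this is the only analysis described that varies their values. The baseline comparison in the Assessment of bias section is useful, but it cannot show whether unobserved grades differ by arm. Readers would take agreement between the two scenarios as evidence of robustness that the scenarios cannot supply.

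**Working it through.** **Inputs from the protocol article**
- Retention r = 0.70 in each arm (Power), so 0.30 missing.
- Filled value v = 0 or 58 points (Primary outcome, Table 1); adjacent pass grades are 6 points apart.
- The Power section equates 0.1 SD with "one-fifth of a GCSE grade or 1.154 points on the 58 points point scale", so SD = 1.154 / 0.1 = 11.54 points.
- Power "is 80% with a significance level of 0.05"; two-sided testing and 1:1 allocation are assumed, as the article states neither.

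**The plan's own figure.** With 154 analysed (77 per arm) and no covariates, the detectable difference is (1.960 + 0.842) × √(2/77) = 0.452 SD. The plan states 0.45 SD, and 0.45 × 11.54 = 5.193 points. This reproduces, so 5.193 points (detectable effect) and 1.154 points (threshold) serve below as example observed differences.

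**Effect of the rule.** With observed means m1 and m0 and retention r1 and r0, each filled arm mean is r × m + (1 − r) × v. The difference is

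r1 × (m1 − v) − r0 × (m0 − v).

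When r1 = r0 = r, this is r × (m1 − m0), whatever v is:
- 0.70 × 5.193 = 3.635 points (0.315 SD), in both scenarios;
- 0.70 × 1.154 = 0.808 points (0.07 SD), in both scenarios.

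**What is left untested.** With equal retention, the full-cohort difference is r × d_obs + (1 − r) × d_mis, where d_obs and d_mis are the arm differences among observed and missing children. Both scenarios set d_mis = 0. If d_mis were 6 points (one grade, an assumed size), the result would move by 0.30 × 6 = 1.8 points, and 1.8 / 11.54 = 0.16 SD. For an observed 1.154 points:
- d_mis = −6 gives 0.808 − 1.8 = −0.992 points (−0.09 SD);
- d_mis = +6 gives 0.808 + 1.8 = 2.608 points (0.23 SD);
- the planned scenarios show 0.808 both times.

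A simulation with 70% retained per arm and opposite selection by arm (assumed) behaved the same way. A spurious observed 0.26 SD, with no true difference, gave 0.18 SD in both scenarios. A true 0.28 SD masked to an observed 0.03 SD gave 0.02 SD in both.

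**Unequal retention.** With an observed 0.1 SD, an assumed control mean of 40 and retention of 75% v 65%:
- lowest grade: 0.75 × 41.154 − 0.65 × 40 = 4.87 points (+0.42 SD);
- highest grade: 0.75 × (41.154 − 58) − 0.65 × (40 − 58) = −0.93 points (−0.08 SD).

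The result moves, but only because the numbers missing differ. The missing in both arms are still given the same grade.

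**Opposed extremes.** Giving one arm 0 and the other 58 adds ±0.30 × 58 = ±17.4 points (17.4 / 11.54 = 1.51 SD). An observed 0.1 SD then runs from 0.808 − 17.4 = −16.592 points (−1.44 SD) to 0.808 + 17.4 = 18.208 points (+1.58 SD).

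**The SD.** If SD_pooled were recalculated on filled data, the standardised result would change again. With an assumed control mean of 40, an observed 0.45 SD becomes 3.635 / 21.81 = 0.167 (lowest) or 3.635 / 12.02 = 0.302 (highest). Over assumed means of 34 to 46, the ranges are 0.150–0.187 and 0.263–0.342.

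**The case against.** **Retention will not be exactly equal.** This stands. The Power section states a planning expectation, and each of the seven trials is analysed separately. A reader might infer that the scenarios can never change the sign of the difference, or can never respond to attrition. The documents do not support that: the cancellation is exact only for the unadjusted difference at equal retention, while the primary model is adjusted, and the 75% v 65% example changes sign. With 309 randomised 1:1 (assumed) and 70% retained, the chance standard error of the retention difference is √(2 × 0.7 × 0.3 / 154.5) = 5.2 percentage points. At a mean of 40, that alone moves the result by about 0.18 SD (lowest) or 0.08 SD (highest). So the rule does react to differing attrition rates. It still does not examine differing outcomes among the missing, and some of its movement would be chance imbalance in numbers.

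**The wording may be shorthand for opposite values by arm.** This is possible in a condensed article, and an unseen analysis plan may say so. But the sentence refers to all missing participants and names no arm. The two readings differ by ±17.4 points, so the assignment needs stating either way.

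**Other safeguards exist.** The baseline comparison, the risk-of-bias assessment and the covariate adjustment all help. Missingness arises largely through record linkage, and the Limitations section expects schooling outside the state sector to have a minimal and non-differential impact. These make a large arm difference among the missing less likely, but none of them tests for one.

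**The illustration is generous.** This also stands. Six points is 6 / 11.54 = 0.52 SD between arms among the missing, more than the detectable 0.45 SD, and nothing in the article supports that size. It shows scale and is not a forecast.

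**Conclusion.** The point holds for the rule as literally written. Under the expected retention, both scenarios scale the unadjusted difference by about 0.70, approximately so after adjustment. Under unequal retention they track the number missing per arm. Neither examines an arm difference in the unobserved grades, so the analysis does not deliver its stated worst-case purpose. An assumed 6-point difference among 30% missing would move the result by 0.16 SD, past the 0.1 SD threshold, without showing in the planned output.

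Two further inferences should be resisted. The article does not expect 30–50% missing: it expects about 30%, and 50% is a conservative example for one trial. Nor is a real effect diluted in the main result, because the primary estimate, interval and test are untouched. The additional shrinkage through the SD depends on an assumed mean and on recalculating SD_pooled, which the article does not state. This is a weakness in a sensitivity analysis that should be corrected before the data are analysed. It is not a flaw in the primary analysis.

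**What to change.** Replace or supplement the rule with an analysis that lets the missing differ by arm:
- Impute missing GCSE mathematics, then add a graded shift to the imputed values in one arm at a time, for example ±3, ±6 and ±12 points (half a grade, one grade and two grades). Extend the grid until the conclusion changes, and report the shift at which it does. As a guide, if the imputed values carry the observed difference and 30% are missing, the point estimate reaches zero at a shift of 1.154 / 0.30 = 3.8 points for an observed 0.1 SD, and 5.193 / 0.30 = 17.3 points for an observed 0.45 SD.
- Show the opposed extremes (intervention lowest with control highest, and the reverse) as outer bounds only. At ±17.4 points they are too wide to inform on their own.
- Hold SD_pooled at its observed-data value throughout.
- If the same-grade scenarios are kept, say that both arms receive the same value and report retention by arm beside them.

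The cost is a few more lines of code and no new data. The bounds will be wider and less reassuring than those now planned.

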#### Assessment of bias

For each trial, we will compile information for a Cochrane risk of bias analysis.^21^

To detect whether selection bias at follow-up has affected the randomisation balance of characteristics, we will present the prerandomisation characteristics as percentage/mean differences between intervention and control groups at randomisation and at age 16 (when the primary outcome is measured) with 95% CIs.

## Discussion

### Expected outcomes of the study

High participant retention rates are essential to determine delayed intervention effects that might not become apparent in short-term follow-ups or when using traditional follow-up methods, which typically suffer from high attrition.^2 22^ Extending follow-up of RCTs without the need for participants to re-engage is possible where trial data and participant identifiers have been retained and governance arrangements allow secure linkage that safeguards participants’ privacy. Post-trial extension using opt-out linkage to administrative data will be especially desirable for future research if it reduces costs associated with conventional methods of follow-up (such as face-to-face interviews) and simultaneously improves participant retention rates (compared with opt-in data linkage). Critically, our study will allow new insights into the long-term cognitive benefits and safety profile of modified infant formulas, by making use of randomised historical infant formula comparisons, which are unlikely to be investigated in future RCTs either due to lack of equipoise or resources.

### Limitations

Our study should be considered in the context of several limitations.

First, only schools following the national curriculum have to contribute data to the NPD, while independent schools may provide data voluntarily.^23^ Some participants who received their education outside state-funded English schools will therefore be excluded from this analysis. In any given academic year, however, data from 99% of all children of compulsory school age are included in the NPD.^9^ Consequently, we expect this to have minimal, non-differential impact on overall linkage success.

Second, there is no general agreement on what defines educational performance and which age is optimal to capture intervention effects. To minimise missing data and detect potential trajectory effects, we will therefore rely on data from two high-stakes examinations sat by the majority of state school students in England.

Third, linkage quality plays a role when using administrative data to follow up participants.^24–27^ The FFT will provide us with up to three different pupil records per participants (based on names, date of birth and location). We will use probabilistic methods adapted from Fellegi and Sunter^28^ as well as manual review to decide which record, if any, we consider to be the best match (online supplementary material).

Fourth, we acknowledge that intervention effects measured 15 years later might be diluted by contextual factors. Convergence of trial arms may result from catch-up over time as those who lag behind in early years might receive extra (eg, educational) assistance. There will also be variability in terms of quality of education. However, this is likely to be roughly equal between intervention and control groups due to adequate sample size, randomisation and blinding. Furthermore, theories of early programming suggest that early postnatal life is a critical period of development^29^ and nutritional stimuli during this period can result in lifelong permanent effects.^30^ If true, any effective nutritional intervention is unlikely to disappear completely by early adulthood. If not, our study should be of increased interest to the scientific community concerned with the early origins of adult health and disease theory. Either way, it will provide important insights for parents, policy makers and the scientific community as to whether choice of infant formula type can have long-lasting, measurable effects on something as important as educational performance.

## Ethics and dissemination

### Ethics approval and legal basis for data processing

The proposal to link the trials and NHS data underwent a robust ethical, legal and technical review. The proposed project was approved by the UCL Research and Development Office and Data Protection Office (Reference: 14PE15), the NHS London-City and East Research Ethics Committee (Reference: 17/LO/0556) as well as the Health Research Authority and Health and Care Research Wales (Reference: 212148). An exemption under Section 251 of the NHS Act 2006 was granted by the Confidentiality Advisory Group (Reference: 17CAG0051) and allows UCL GOS ICH and the FFT to process identifiable participant information to facilitate the data linkage and analyses without consent. Dissent and fair processing were discussed with the HRA CAG and an opt-out procedure is in place.^31^

### Confidentiality

Special efforts are made to protect participant privacy and confidentiality. All linked data will be de-identified and thus contain no information on personal identifiers such as names and addresses. Identifiers will be stored at separate access-restricted locations certified to international standards (ISO/IEC 27001). Access to all data will also be physically restricted. Analysis data will be stored as aggregated as possible (such as school types instead of school IDs), to minimise the risk of re-identification. All analyses will be conducted in a digital safe haven and no individual-level data is allowed to leave the server. Outputs will have to meet statistical disclosure controls that prevent small cell sizes to be exported from the server. Additionally, access to the data will be restricted to an authorised group of researchers, who will all have undergone the HSCIC and ADRN information governance training and are bound by their university contracts to treat the data confidentially.

### Dissemination of results and publication policy

To enhance the use, understanding and dissemination of this study, the results will be disseminated to both scientific and lay audiences, submitted for publication in peer-reviewed journals, and will contribute towards a PhD dissertation.
